## Abstract

**Background:**

Stroke is the principal cause of permanent disability in adult age, and many patients require lifelong medical treatment and care from others for their daily activities. It has enormous repercussions on the work and social lives of patients and their families and involves major economic expenditure. Post-stroke spastic upper limb is usually treated with rehabilitation, occupational therapy, and periodical injections of botulinum toxin, while surgical correction is now seldom considered. However, there has been no clinical trial to compare between surgical and toxin treatments. The primary aim of this study is to compare outcomes between surgery and a conventional approach with botulinum toxin in patients with post-stroke upper limb spasticity.

**Methods:**

A two-arm (surgical treatment [n = 22] *vs*. botulinum toxin [n = 22]) randomized clinical trial (RCT) will be performed to compare the efficacy of surgery with that of botulinum toxin treatment in patients with post-stroke upper limb spasticity. Data will be collected at baseline and at 6 and 12 months of follow-up on functionality, hygienic status, quality of life, sleep quality, anxiety/depression levels, and functional magnetic resonance imaging (fMRI)-measured brain activity. Healthcare and care costs will be compared between the groups.

**Discussion:**

This research is set in the context of chronic diseases, aging, and functional/mobility limitations. The results can be expected to have a major impact, because the high prevalence of stroke and the severe associated disability means that an enormous number of patients can benefit from improved treatment protocols, and a more rational use of resources would yield considerable economic benefits for health and care systems. Our expectation is that outcomes would be more favorable with surgery. However, the aim is not to exclude any approach but rather to explore how the potential and indications of each treatment could be integrated within a multidisciplinary therapeutic protocol in a complementary manner.

**Trial Registration**: ClinicalTrials.gov (NCT06392633). Registered on 30 April 2024.

## Introduction

Stroke is associated with high mortality and morbidity rates and represents a public health problem of the first order. It is the main cause of permanent disability in adult age [1] and responsible for spasticity in 38% of patients, who require chronic medical treatment and depend on others for their daily living activities [2], with a severely impaired quality of life [3].

Population aging and improved stroke survival rates have raised the number of individuals with stroke sequelae needing specialist care, rehabilitation, and support, increasing the burden on families, society, and health systems [4]. Although there have been improvements in the management of acute stroke episodes, less attention has been paid to the chronic care of sequelae, leading many patients to feel abandoned after their discharge from hospital, with the need to manage and defray their care needs themselves due to inadequate support from the public healthcare system. Caregivers play a key role in the care of stroke survivors, and it is important to capture and predict changes in caregiver quality of life and burden for the design of tailored interventions [5].

Various surgical techniques are applied to optimize the function, reduce the pain, and improve the hygiene and esthetics of the spastic upper limb [6]. Corrections can be performed by single-event multilevel surgery, with a combination of soft tissue releases and elongations, tendon transfers, and joint stabilization procedures [7], or by focusing on the nerve as spasticity vehicle and using hyponeurotization or hyperselective neurectomy [8] or even rhizotomy of the C7 root with contralateral transfer [9–11].

Currently, the first-choice treatment of localized spasticity is intramuscular injection of botulinum toxin A [12,13]. This has generally replaced surgery, which is now seldom considered and may be under-prescribed [14,15], although no studies have compared these modalities.

Surgery for upper limb spasticity has been associated with high satisfaction levels in patients and caregivers and with low complication rates [16]. Although it cannot be performed in many patients, good long-term outcomes have been reported for the surgical treatment of non-functional or hygienic upper limbs, [7,17]. However, scientific evidence of its effectiveness remains weak, generally based on retrospective case series with no control group or on heterogeneous study populations of patients with stroke, child cerebral palsy (CCP), or post-traumatic brain injury (TBI), among others.

The success of therapeutic procedures has usually been evaluated in terms of outcomes from the perspective of the physician. Less attention has been paid to the impact of the disease on daily life, social functioning, and patient satisfaction or to the predicted utilization of health resources. However, increasing consideration is being given to the evaluation of outcomes from the perspective of patients [18], including quantification of their own perception of their health and the impact of symptoms or treatments on health-related quality of life (HRQOL). HRQOL is a multidimensional concept that combines physical, mental, emotional, and social functioning with wellbeing [19]. Information from patients can be useful for the design and implementation of interventions by health teams, for comparison of the effectiveness of different treatments (e.g., medical *vs*. surgical), and for the modification of surgical techniques, among others.

Some studies have assessed the impact of therapy with rehabilitation and botulinum toxin on the quality of life of patients with stroke [20,21], but only Van Heest et al. [22] have examined the effects of a surgical approach on quality of life, and their study population comprised pediatric patients with CCP, whose profile differs from that of stroke patients.

The application of functional MRI (fMRI) in patients with stroke sequelae allows the recovery of motor functions to be monitored and brain activity to be compared with that of healthy controls [23], correlating post-treatment findings with improvements in social ability, expression, and cognitive capacity [24].

Besides the peripheral effects of botulinum toxin treatment, it has been associated with brain modulation in fMRI studies of patients with stroke [25,26] or TBI [27]. However, fMRI has not been used to investigate changes that may result from spastic hand surgery, except in the trial by Zheng et al. on contralateral C7 nerve root transfer [11].

Randomized clinical trials (RCTs) are required to compare outcomes, economic cost, and impact on quality of life between the surgical and botulinum toxin treatment of patients with post-stroke upper limb spasticity.

## Materials and methods

This protocol follows the Standard Protocol Items by Recommendations for Interventional Trials (SPIRIT) checklist and diagram (Table 1).

**Table 1 pone.0322588.t001:** Details of enrollment, interventions and assessments following the SPIRIT diagram. MRI: Magnetic Resonance Imaging.

	STUDY PERIOD				
	Enrolment	Allocation	Post-allocation		Close-out
TIME POINT	0-90 days before	0	Baseline	6 months	12 months
ENROLMENT					
Eligibility Screening	X				
Informed consent		X			
Initial evaluation	X				
Allocation		X			
INTERVENTIONS					
Surgery					
Botulinum Toxin					
ASSESSMENT					
** *Baseline* **					
Clinical and sociodemographic data			X		
Functionality evaluation			X	X	X
Caregiver burden evaluation			X	X	X
Quality of life evaluation			X	X	X
Sleep, anxiety, and depression assessments			X	X	X
Structural and functional MRI			X	X	X
*Outcome variables*					
Changes in functionality				X	X
Changes in caregiver burden				X	X
Changes in quality of life				X	X
Changes in sleep quality, anxiety, and depression				X	X
Structural changes (gray and white matter) on MRI				X	X
Functional changes on MRI				X	X

### Aims, design, and setting

The primary aim of this study is to compare outcomes between surgery and a conventional approach with botulinum toxin in patients with post-stroke upper limb spasticity.

The secondary aims are:

To compare functional and hygienic changes (non-functional: esthetics, pain, and ease of care) in the spastic upper limb between surgery and botulinum toxin therapy using the House [28], Fugl Meyer [29], GAS [30], Zancolli [31], Modified Ashworth-Bohanon [32], Keenan [33] and the pain Visual Analog Scale (VAS) [34]To compare the impact on quality of life related to care and psychosocial risks of surgery *versus* botulinum toxin therapy in patients with post-stroke upper limb spasticity using SF 36 [35] and the Newcastle stroke-specific quality of life measure [36]To compare the effects on sleep quality (PSQI) [37], anxiety and depression (HADS) [38] of surgery *versus* botulinum toxin therapy in patients with post-stroke upper limb spasticity.To compare the effects on caregiver burden of surgery *versus* botulinum toxin therapy using the Zarit [39] and Caregiver Burden scales [7].To compare the effects on brain structure and function of surgery *versus* botulinum toxin therapy using fMRI.To perform a comparative cost-effectiveness analysis between patients with stroke sequelae treated with surgery *versus* botulinum toxin therapy.

The study will be a two-arm RCT in patients with post-stroke upper limb spasticity, randomly assigning participants to a Control group for botulinum toxin treatment or an Experimental Group for surgery (1:1 allocation ratio).

It will be conducted in Granada (940,974 inhabitants) and Jaén (620,242 inhabitants), two cities in in southern Spain, and will be led by Clínico San Cecilio University Hospital (CSCUH), Ciudad de Jaén University Hospital (CJUH), and the Surgery Department of Granada University.

The Project for this trial (Ref: PI20/01574) is funded by the *Instituto de Salud Carlos III* (ISCIII) and co-funded by the European Union. This research is part of the doctoral thesis of [name], developed under the Doctoral Program in Clinical Medicine and Public Health at the University of Granada (Spain).

A sample of 44 adults with post-stroke spastic upper limbs will be recruited for the study between 1^st^ January 2023 and 30^th^ June 2025.

### Participants

Participants will be recruited according to the following inclusion criteria: a) age > 18 years, b) presence of post-stroke upper limb spasticity, c) minimum time interval of 12 months since the stroke, d) agreement to surgery for upper limb spasticity and inclusion on the hospital surgical waiting list, and e) written informed consent to participation in the study (by the patient or legal representative). Exclusion criteria will be anesthetic risk (ASA) ≥IV, presence of involuntary (extrapyramidal) movements, inability to adequately respond to questionnaires, the presence of deformities not treatable by surgery, and the impossibility of follow-up at a minimum of 12 months. (Fig 1).

**Fig 1 pone.0322588.g001:**
[figure not shown]
Overview of the study.

Any patient who starts the study can abandon it at any time due to health, administrative or travel problems.

The sample size has been estimated for 5% type I error probability, 80% power, and a large effect size difference (0.8 standard deviations). Balanced one-way analysis of variance power calculation yielded K = 2, n = 16.71472, and f = 0.5. Accordingly, 34 patients (17 per group) are required with a minimum follow-up of 12 months. The sample size is set at 44 patients (22 patients in each group) to cover possible losses to the follow-up of 20%.

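### The sample size is stated for a 0.8 SD difference but was calculated for 1.0 SD (f = 0.5); for 0.8 SD, 17 completers per arm give about 62% power, not 80%.

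*Protocol article*

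**What the plan says.** The sample-size paragraph is in the protocol article under Materials and methods, Participants, just after the Fig 1 caption. It opens with the design targets: "The sample size has been estimated for 5% type I error probability, 80% power, and a large effect size difference (0.8 standard deviations"). The next sentence gives the calculation: "Balanced one-way analysis of variance power calculation yielded K = 2, n = 16.71472, and f = 0.5". From this it concludes: "Accordingly, 34 patients (17 per group) are required with a minimum follow-up of 12 months". The total is then raised to 44 (22 per arm) to allow for 20% loss to follow-up.

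Allocation is 1:1 (Aims, design, and setting). The Data analysis section plans Student's t-test, or Mann-Whitney U for non-normal data, for continuous outcomes between groups. Repeated-measures regression is reserved for within-group change. Nothing elsewhere in the article connects f = 0.5 with 0.8 SD.

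**The concern.** Two adjacent sentences give two different effect sizes. The first describes "a large effect size difference (0.8 standard deviations"); the second uses f = 0.5. For two groups of equal size, f and the standardised mean difference d are tied by f = d/2, so both statements cannot describe the same design.

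This paragraph is the only justification the article gives for the size of the trial. If 0.8 SD is the effect of interest, as the wording suggests, the type II error at the planned number of completers is 38% rather than the stated 20%. A reader who takes the paragraph at face value could treat a non-significant result as fair evidence against a 0.8 SD benefit of surgery, when the design has nearly a 4 in 10 chance of missing one.

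**Working it through.** **Inputs from the protocol article**
- Type I error 5%, power 80%, difference 0.8 SD (Participants, sample-size paragraph)
- K = 2, f = 0.5, n = 16.71472 per group (same paragraph)
- 17 evaluable per group, 20% loss, 22 recruited per group (same paragraph)
- 1:1 allocation (Aims, design, and setting)
- t-test between groups (Data analysis)

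Sidedness is not stated in words. The F test with K = 2 is equivalent to a two-sided t-test, and the printed n reproduces on that basis.

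**Step 1. Convert the effect sizes.** With two equal groups whose means differ by d SD, each mean lies d/2 from the grand mean, so f = d/2.
- Stated effect: d = 0.8 gives f = 0.8/2 = 0.4.
- Effect used: f = 0.5 gives d = 2 × 0.5 = 1.0.

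**Step 2. Reproduce the plan's figure.** Power = P(F′ > F crit), where F′ is noncentral F with 1 and 2(n − 1) degrees of freedom and noncentrality K·n·f². Solving for 80% power at alpha = 0.05:

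| f | d | n per group |
|---|---|---|
| 0.5 | 1.0 | 16.71472 |
| 0.4 | 0.8 | 25.52 |

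The first row matches the article to all printed digits. A two-sided t-test with d = 1.0 gives the same 16.71472. The calculation was therefore run for 1.0 SD.

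**Step 3. Power of the planned design.** Two-sided noncentral t, 2n − 2 degrees of freedom, noncentrality d·√(n/2). For n = 17 and d = 0.8, the noncentrality is 0.8 × √8.5 = 2.33.

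| Completers per arm | Power for 0.8 SD | Power for 1.0 SD |
|---|---|---|
| 17 | 61.9% | 80.7% |
| 22 (no loss) | 73.6% | 90.0% |
| 26 | 80.7% | 94.2% |

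The smallest difference detectable with 80% power is 0.99 SD with 17 per arm and 0.86 SD with 22.

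**Step 4. What 0.8 SD at 80% would have required.** 25.52 rounds up to 26 completers per arm, 52 in total. After 20% loss, 26/0.8 = 32.5, so 33 per arm and 66 in total.

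**Step 5. Check the loss allowance.** 17/0.8 = 21.25, so 22 per arm and 44 in total. This step is correct and is not part of the error.

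**Step 6. Could a one-sided test explain it?** For d = 0.8, a one-sided 5% test needs 20.03 per arm and has 73.8% power at 17. It passes 80% only if all 22 per arm also complete (83.3%). A one-sided reading does not yield the printed n for 0.8 SD.

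**Step 7. Could baseline adjustment close the gap?** If r is the correlation between baseline and 12 months, adjustment multiplies the residual variance by (1 − r²). Replace d with 0.8/√(1 − r²) and use 2n − 3 degrees of freedom. The article gives no r, so the values below are assumptions. At 17 per arm:

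| Assumed r | Power for 0.8 SD |
|---|---|
| 0.3 | 66% |
| 0.5 | 74% |
| 0.6 | 81% |
| 0.7 | 89% |

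Adjustment restores 80% only if r is about 0.6 or higher.

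**The case against.** The arithmetic is hard to dispute, but four qualifications deserve a hearing.

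- **The intended effect is not certain.** If 1.0 SD was meant, the design has 80.7% power at 17 per arm and only the label is wrong. That is possible, though the article pairs the word large with 0.8 SD, which makes 0.8 the natural reading. The paragraph is wrong under either reading.
- **62% is the lower of two figures.** It assumes the loss allowance is fully used. With no loss, power is 74%. That is fair and both should be quoted, but neither reaches 80%.
- **No outcome is attached to the calculation.** The functionality evaluation, labelled the main variable, comprises five instruments, several of them ordinal. The analysis also allows rank and categorical tests and a correction for multiple comparisons. The 62% applies to an unadjusted t-test on one continuous outcome at 5%. This limits how precisely power can be stated for the real analysis; it does not rescue the stated 80%.
- **The practical effect is limited.** Recruitment began in January 2023 and was expected to finish around June 2025, so the sample size is largely settled. The article also does not say how a null result would be interpreted. This bears on the remedy, which should not ask for more patients. It does not excuse printing a power figure that belongs to a different effect.

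**Conclusion.** The paragraph is wrong as written. Its 80% power belongs to a 1.0 SD difference, not the stated 0.8 SD. For 0.8 SD the design has 62% power with the planned 17 completers per arm and 74% with all 22, against the 26 completers per arm needed for 80%. These figures assume a two-sided 5% test, equal arms and an unadjusted t-test on a single continuous outcome. The first two match the article's own calculation, and the t-test is its planned between-group method. The conclusion is firm because the printed n reproduces exactly at f = 0.5 and nothing else in the article reconciles the two effect sizes.

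**What to change.** Correct the sample-size paragraph and keep 44 patients. State that 17 completers per arm give 80% power, at two-sided 5%, for a difference of about 1.0 SD, and give the power for 0.8 SD alongside: 62% with 17 completers per arm and 74% if all 22 are retained. If 1.0 SD is kept as the design effect, add a sentence on why a difference of that size is plausible. The cost is one rewritten paragraph and a less favourable power statement, with no additional patients.

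An alternative is to keep 0.8 SD and restate power under a baseline-adjusted between-group comparison. This costs more: the Data analysis section would have to replace the planned t-test with that analysis, and the assumed baseline to 12-month correlation would have to be stated and justified. At 17 per arm it reaches 80% only at a correlation of about 0.6 or more, so the power should be shown over a range that includes lower values.

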### Ethics approval and consent to participate

This study has received approval from the clinical research ethics committee of the Junta de Andalusia (Spain) on 7 December 2020 (code: 6hWMS793PFIRMAj6fT0fx7yTDkZ6SF). Authors have intentions to obtain informed consent to participate in the study from participants (both documents are sent as additional files). Patient participation will be entirely voluntary. They will sign the corresponding informed consent in accordance with ethical criteria in the 2013 modification of the Helsinki Declaration for the performance of research projects and with national legislation on clinical trials (Law 29/2006 26 July, modified in July 2013). The confidentiality of study material will comply with national legislation on personal data protection and digital rights (Law 3/2018, 5 December).

### Recruitment

[name] will prepare a list of patients with stroke sequelae for > 1 year from the records of the Rehabilitation Departments of the Granada and Jaen University Hospitals (Andalusia, Spain) and from associations of patients with acquired brain damage (ADACEA [Jaen], NEUROAFEIC, and AGREDACE [Granada]). A Rehabilitator ([name], [name], [name]) on the research team will contact candidate participants to explain the study, confirm eligibility, and obtain informed consent.

At enrolment, a clinical assessment of all participants will be performed by a Rehabilitator at the CSCUH to verify the diagnosis and confirm that eligibility criteria are met. The clinical assessment consists of a neurological examination and a short, standardized medical history interview. Baseline data will be collected at this session.

Before randomization, all selected patients will be examined by a hand and upper limb surgeon ([name]) for assessments of the shoulder, elbow, wrist, and hand, using peripheral nerve blockade anesthetics when required. Patients will receive individualized proposals for single-event surgery with a combination of soft tissue procedures (tenotomy, tendon lengthening, or tendon transfer), selective neurectomies, and bone procedures (osteotomy and arthrodesis).

### Randomization

Randomization of patients will be conducted by an independent member of the research team ([name]) not involved in the data collection. The allocation sequence will be based on a computer-generated random number. Randomization will be conducted after the recruitment of individual participants is completed to reduce the risk of selection bias.

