### Data collection

Evaluations will be conducted by a specialist physician with >25 years’ experience at three time points: at baseline (t0) and at 6 months (t1) and 12 months (t2) post-intervention. Evaluations will be carried out in single sessions at Granada University School of Medicine except for the fMRI scan, which will be performed at the Mind, Brain, and Behavior Research Center of the University of Granada by technical staff at this center. (Fig 1).

Data will be collected on the following clinical and sociodemographic variables: age, sex, type of stroke, date of stroke, interval between stroke and treatment, gait capacity on the Functional Ambulation Classification (FAC) scale [40], upper limb lesion (functional or hygienic), cognitive status [41], family support, need for assistance (Barthel index) [42], and anesthetic risk (ASA) [43], classifying upper limb lesions as functional or hygienic hand and categorizing elbow, wrist, and hand deformities according to Keenan et al [33].

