This research is set in the context of chronic diseases, aging, and functional/mobility limitations. The results can be expected to have a major impact, because the high prevalence of stroke and the severe associated disability mean that an enormous number of patients can benefit from improved treatment protocols, and a more rational use of resources would yield significant economic benefits for health and care systems.

We anticipate that the findings of this RCT will contribute to our understanding of the role of upper limb surgery for spasticity in combination with conventional therapy. They will also provide evidence on the specific target group of patients who could gain most from surgery and on the safest and most appropriate procedures to consider. Future results will be communicated through articles in high-impact journals and international conferences on traumatology, rehabilitation and neurology.

The RCT design is a major strength of this study. On the other hand, it will be limited to a specific geographical area and to the public health sector, which may hinder the extrapolation of results to other populations. Other expected limitations include the heterogeneous nature of stroke patients in terms of their baseline injury and upper limb sequelae. In addition, the surgery will not be a single procedure but will involve different steps according to the needs of the patient, making analysis more complex. Multivariate analysis of the applied techniques may be required. The quality of life and psychosocial repercussions are not the only variables that could be selected, and functional and quality of life outcomes are influenced by environmental conditions and patient characteristics such as tiredness, cognitive level, and expression ability. Exclusion criteria have been selected to minimize these influences. Economic analyses may also over- or under-estimate costs, and it can be highly challenging to quantify all informal, secondary, or indirect costs. Nevertheless, information on the economic impact of diseases and their treatments is crucial for health policy planning and evaluation.

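### The article does not say how the 22-per-arm split is secured; limb type is left to chance in the allocation, and the stated between-arm tests do not adjust for it

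*Protocol article*

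**What the plan says.** The Randomization section of the protocol article describes the sequence in one sentence: "The allocation sequence will be based on a computer-generated random number". It adds on timing: "Randomization will be conducted after the recruitment of individual participants is completed to reduce the risk of selection bias". An independent team member carries this out.

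The arm sizes are given as fixed. The Aims, design, and setting section has "Experimental Group for surgery (1:1 allocation ratio", and the sample size paragraph under Participants has "The sample size is set at 44 patients (22 patients in each group". The abstract repeats 22 and 22. Blocks, strata, minimisation and a balanced list are not mentioned anywhere, and neither is unrestricted allocation.

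The Data collection section lists "upper limb lesion (functional or hygienic" among the clinical variables recorded. The Discussion names as a limitation "the heterogeneous nature of stroke patients in terms of their baseline injury and upper limb sequelae".

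For between-group comparisons, the Data analysis section plans Student's t-test, or Mann-Whitney when data are not normal, and McNemar or Fisher tests for discrete scales. The repeated-measures regression there is for changes within a group. The multivariate regression relates functional improvement to quality of life. Neither is an adjusted comparison of the arms.

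**The concern.** Two things do not join up. First, exact arm sizes are stated, but the one sentence on method would not by itself deliver them. Second, the main variable is functionality (House, Zancolli and Fugl-Meyer among other scales), and whether a limb is functional or hygienic plausibly bears on how far such scores can move. The article records that factor and acknowledges heterogeneous limbs, yet ties it neither to the allocation nor to the arm comparison.

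With 44 patients, a sizeable chance difference in limb mix is possible. An unadjusted test still keeps its error rate over repeated randomisations. But in the one trial that is run, an observed imbalance would make the functional comparison harder to interpret, and precision that a recorded covariate might give is not used.

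**Working it through.** **The plan's own figure.** Inputs, from the sample size paragraph: "5% type I error probability, 80% power, and a large effect size difference (0.8 standard deviations" and "Balanced one-way analysis of variance power calculation yielded K = 2, n = 16.71472, and f = 0.5". Solving the balanced one-way ANOVA for k = 2, f = 0.5, alpha 0.05 and power 0.80 gives 16.7147 per group, which reproduces the stated n. Rounded up, this is 17 per group, and 17 / (1 − 0.20) = 21.25, so 22 per arm and 44 in all. With two equal groups f = d/2, so f = 0.5 is a difference of 1.0 SD, while the stated 0.8 SD is f = 0.4. That mismatch is a separate matter; power is shown below at both values.

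**Arm sizes if allocation is simple.** The size of one arm is Binomial(44, 0.5).

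- Exactly 22/22: C(44, 22) / 2^44 = 0.120, so the split is missed with probability 0.880.
- 18/26 or worse: 0.291.
- 16/28 or worse: 0.096.

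**Power cost of unequal arms.** Two-sided t-test, 42 degrees of freedom, all 44 analysed, noncentrality d × √(n1·n2/44). The square root is √11 = 3.317 at 22/22 and √(448/44) = 3.191 at 16/28.

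| Split | d = 1.0 | d = 0.8 |
|---|---|---|
| 22/22 | 0.900 | 0.736 |
| 18/26 | 0.890 | 0.722 |
| 16/28 | 0.876 | 0.703 |
| Average under simple randomisation | 0.893 | 0.726 |

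The average loss is 0.007 at d = 1.0 and 0.010 at d = 0.8. Even 16/28 costs only 2 to 3 points.

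**Limb-type imbalance.** The share of functional limbs is not in the article, so 20% to 50% is assumed: F = 9, 13, 18 or 22 of 44. Under simple randomisation, K ~ Binomial(F, 0.5) functional and M ~ Binomial(44 − F, 0.5) hygienic limbs fall in arm 1. The gap is |K/(K+M) − (F−K)/(44−K−M)|. With 22/22 forced but no strata, K is hypergeometric and the gap is |2K − F|/22.

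| Functional limbs (of 44) | P(gap ≥ 20 points), simple | P(gap ≥ 20 points), 22/22 forced |
|---|---|---|
| 9 | 0.104 | 0.132 |
| 13 | 0.160 | 0.185 |
| 18 | 0.200 | 0.124 |
| 22 | 0.178 | 0.131 |

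The forced column is uneven because counts are discrete: 20 points of 22 is 4.4, so |2K − F| must reach 5 when F is odd and 6 when F is even.

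The risk is therefore about 10% to 20% under simple randomisation, and about 12% to 19% with equal arms forced. Blocks alone do not remove it; strata, or adjustment in the analysis, deal with it.

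**The case against.** The strongest reply is that simple randomisation is an inference. A shuffled list of 22 and 22 labels, or permuted blocks, also starts from computer-generated random numbers, and the stated 1:1 ratio and equal arms point towards such a list. The timing sentence can be read patient by patient, or as a single draw once everyone is recruited, where 22/22 is easily forced. Block sizes and strata are details that an article commonly leaves to the full protocol. All of this stands. A reader might infer that the trial uses plain, unrestricted randomisation; the article does not establish that.

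A reader might also infer that the limb types will be unbalanced. They need not be: on the assumed shares, a gap below 20 points has a probability of about 80% or more.

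A further tempting step puts a size on the bias. If limb types differ by 1 to 1.5 SD, a 20-point gap moves the arm difference by 0.20 × 1 = 0.20 to 0.20 × 1.5 = 0.30 SD, or 25% to 38% of 0.8 SD. The article gives no such difference. Table 2 defines the functional outcome as a change, so the 1 to 1.5 SD would have to hold for change scores; a difference that lies only in baseline level cancels. That figure should not be used.

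It is also not settled that limb type is known before allocation. The Recruitment section places baseline data at the enrolment session, whereas Table 1 puts clinical data in a baseline column under post-allocation. The surgeon's examination precedes randomisation, but the article does not say that it assigns limb type.

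Finally, small blocks carry a risk when clinicians can see who had surgery and who had injections: later assignments in a block may be guessed.

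What survives is that the Data analysis section does name the between-arm tests, and those named are unadjusted. Covariate adjustment answers the limb-type point however the sequence was made.

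**Conclusion.** The point holds in a limited form. The article states equal arms without saying what secures them. If allocation is simple, 22/22 occurs 12% of the time, but the average power loss is only about 1 percentage point, so this is a gap in reporting and consistency and not a power problem. It vanishes if a balanced list was used.

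Limb-type balance is left to chance as far as the article shows. A gap of at least 20 percentage points has a probability of about 10% to 20%, resting on an assumed functional share of 20% to 50%. How much such a gap would move the result cannot be worked out from the article. The between-arm tests as stated make no use of a factor that is already collected, and that can be improved at almost no cost.

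**What to change.** **Analysis (available whatever the state of recruitment).** In the Data analysis section, replace the unadjusted between-arm comparison of functional scores with a regression or ANCOVA containing arm, limb type (functional or hygienic) and the baseline score. For ordered grades such as House, an ordinal regression with the same covariates is the counterpart. Use the limb type classified before treatment, ideally before allocation. The cost is a sentence and two degrees of freedom: with 34 completers, residual degrees of freedom go from 34 − 2 = 32 to 34 − 4 = 30.

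**Allocation (only for patients not yet allocated).** Provided limb type is classified before allocation, use a list stratified by limb type, with varying block sizes (for example 2 and 4) concealed from recruiters. Incomplete last blocks of up to 4 in two strata can still leave a total difference of up to 2 + 2 = 4 patients (20/24), where power is 0.733 against 0.736 at d = 0.8. The drawback is some predictability where treatment is visible. If few patients remain, the benefit is small and the analysis change suffices.

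**Reporting.** In the Randomization section, state whether the sequence is simple or restricted, how 22 per arm is reached, whether the draw is per patient or in one batch, and when limb type is classified.
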